# Evaluating the effectiveness and utility of a novel culturally-adapted telemonitoring system in improving the glycaemic control of Asians with type-2 diabetes mellitus: a mixed method study protocol

**DOI:** 10.1186/s13063-021-05240-6

**Published:** 2021-04-26

**Keywords:** Diabetes, Diabetes mellitus, Telehealth, Telemedicine, Tele-monitoring, Tele-management, Primary care, Culturally adapted, Randomised controlled trial

## Abstract

**Background:**

Regular supervision of patients with type-2 diabetes mellitus (T2DM) by healthcare providers is essential to optimise their glycaemic control but is challenging to achieve in current care models. Telemonitoring is postulated to bridge this gap by leveraging on internet-of-things and mobile-health technology. This study aims to determine the effectiveness of a novel telemonitoring system (OPTIMUM) in improving the glycaemic control of patients with T2DM compared with standard of care alone.

**Methods:**

This mixed-method study comprises an initial randomised controlled trial involving 330 Asian adults with T2DM, aged 26–65 years old with an HbA1c of 7.5–10%, with 115 in the intervention and control arms each. Those in the intervention arm will use standardised Bluetooth-enabled devices to transmit their capillary glucose, blood pressure and weight measurements to the OPTIMUM system. Primary care physicians and nurses will remotely supervise them according to an embedded management algorithm for 6 months, including tele-education via weekly videos over 8 weeks and asynchronous tele-consultation if abnormal or absent parameters are detected. Patients in both arms will be assessed at baseline, 6, 12 and 24 months post-recruitment. The primary outcome will be their HbA1c difference between both arms at baseline and 6 months. Blood pressure and weight control; quality of life, medication adherence, confidence in self-management, diabetic literacy and related distress and healthcare utilisation using validated questionnaires; and incident retinal, renal, cardiac and cerebrovascular complications will be compared between the two arms as secondary outcomes at stipulated time-points. Intervention arm patients will be interviewed using qualitative research methods to understand their experience, acceptance and perceived usefulness of the OPTIMUM system.

**Discussion:**

Overall, this study seeks to evaluate the effectiveness of cultural-adapted telemonitoring system in improving glycaemic control of Asians with type-2 diabetes mellitus compared to standard of care. The results of this trial will better inform policy makers in adopting telemedicine for population health management.

**Trial registration:**

ClinicalTrials.gov NCT04306770. Registered on March 13, 2020.

**Supplementary Information:**

The online version contains supplementary material available at 10.1186/s13063-021-05240-6.

## Background

Worldwide, the number of people living with type-2 diabetes mellitus (T2DM) has quadrupled since 1980 [1]. From 1980 to 2014, the global age-standardised T2DM prevalence has increased from 4.3% to 9.0% [2]. Asia is now the epicentre of the T2DM epidemic and associated cardiovascular complications are the leading cause of morbidity and mortality [3]. In Singapore, the age-adjusted prevalence of T2DM (10.5%) is higher compared to the mean prevalence globally (8.8%) and in South-East Asia (8.5%) [1].

The majority (60%) of patients with TD2M in Singapore are managed at the 18 government primary care clinics or polyclinics due to subsidised fees for consultation, investigations and treatment [4]. T2DM is the third commonest diagnosis in the polyclinic attendances in 2019 [5]. Each polyclinic, staffed by primary care physicians and nurses, provides comprehensive healthcare services, including in-house laboratory, pharmacy, nurse-led retinal and feet screening services to detect T2DM-related complications [4]. Patients with T2DM can walk in or arrange appointments to access the polyclinic services. The current care delivery model comprises on-site clinical and laboratory measurements (such as glycated haemoglobin (HbA1c), lipid and renal panels), counselling and consultation with the polyclinic physicians, nurse clinicians, dieticians and pharmacists in an ambulatory outpatient setting. Aside from a lack of a T2DM register, patients can access multiple healthcare providers. Continuity of care for these patients remains a challenge due to defaulting treatment and a lack of supervision and monitoring in between consultations.

The care delivery system to these patients requires urgent review and enhancement [6], especially with their rising concern to access healthcare services amidst the current COVID-19 pandemic [7]. With the advancement of the internet-of-things, mobile-health, information and communications technology (ICT), their applications in telemedicine can potentially transform the care delivery to these patients [8]. Over the past decade, telemedicine has emerged as a promising solution to bridge the episodic T2DM management.

Telemedicine refers to the systematic provision of healthcare services over separate environments via ICT [9]. In Singapore, it is categorised into tele-collaboration, tele-treatment, telemonitoring and tele-support [9]. A meta-analysis has shown that telemedicine (used interchangeably with telehealth) is effective in improving glycaemic and blood pressure control [10]. However, the selected trials enrolled subjects with baseline HbA1c levels of above 9%, which is skewed towards a subset of high-risk patients and may not be generalisable to others with better glycaemic control. Other limitations include lack of differentiation of the various components of telemedicine and that the study populations were mostly Caucasians. The findings may not be entirely translatable to Asians due to varying levels of acceptance of telemedicine. Sin et al. have shown that only 52% of local patients in polyclinics were willing to use telemonitoring to support their self-management of T2DM and/or hypertension [11]. The construct and design of the telemedicine system need to be patient-centric and culturally-adapted to increase uptake before assessing its outcomes.

A team of primary care professionals have teamed up with a multinational telemedicine vendor to create a telemonitoring system leveraging on the latter’s *VitalHealth* population health platform. Design-thinking, which includes patients’ input, was deployed in developing the telemonitoring system, embedded with educational material, such as locally produced video on T2DM management and evidence-based management algorithm. The system is named OPTIMUM – “*O*ptimising care of *P*atients via *T*elemedicine *I*n *M*onitoring and A*u*gmenting their control of Diabetes *M*ellitus”.

The overarching aim of this mixed-method study is to assess the effectiveness of the OPTIMUM telemonitoring system in improving diabetic management of patients with T2DM by supporting and enhancing their self-management. It includes a randomised control trial (RCT) to compare the glycaemic control, based on the magnitude of HbA1c change at recruitment and at 6th-month post-enrolment, among patients with T2DM in the intervention arm with those in the control arm. The secondary aims include a comparison of blood pressure and weight control; quality of life, medication-adherence, confidence in self-management, diabetic literacy and related distress and healthcare utilisation using validated questionnaires; and incidences of emerging retinal, renal, coronary and cerebrovascular complications of the patients in the two arms at stipulated time-points over 24 months. The study also aims to understand the patients’ experience, acceptance and perceived usefulness of the OPTIMUM system in the intervention arm using qualitative research methods.

## Methods/design

### Study design

The mixed-method study will begin with an open-label, two-arm, superiority, parallel-group RCT of adult ambulatory patients with T2DM who are managed in primary care. It is followed by qualitative research to gather and understand the perspectives of patients in the intervention arm using in-depth interviews. The study protocol conforms to the Standard Protocol Items Recommendations for Interventional Trials (SPIRIT) checklist and is provided as Additional file 1. The flow diagram to summarise the design of OPTIMUM study is in Fig. 1. The RCT was registered at ClinicalTrials.gov in March 2020 (NCT04306770).

**Fig. 1 Fig1:**
[figure not shown]
Overview of trial flow

### Setting and participants

The trial will be conducted at a polyclinic located in Sengkang, an estate in north-eastern Singapore with a population of about 300,000 multi-ethnic Asian residents [12]. This polyclinic serves approximately 900 to 1000 patients daily during office hours in each weekday and is similar to the other polyclinics in Singapore [11]. Current standard of care of patients with T2DM at polyclinics include 3–6 monthly doctor’s consultation with HbA1c readings; fasting laboratory panel tests (electrolyte panel, lipid panel, liver panel and urine albumin-creatinine ratio) at diagnosis and then every 6 to 12 months; and annual diabetic retinal photograph and diabetic foot screening. Patients may be referred to dieticians for dietary advice, nurses for co-management or onwards to tertiary care specialists at the discretion of the attending physician.

### Screening

The study team members will pre-screen patients who have the fasting panel tests as described above for eligibility and advise the attending physician to approach them for study enrolment during their medical review a week after the laboratory test.

### Eligibility for study enrolment

Patients will be screened for the following eligibility criteria.

#### Inclusion criteria

Diagnosis of T2DM in the patient’s electronic medical record (EMR),Latest glycaemic control based on HbA1c reading between 7% and 10%,Age between 26 and 65 years,No or only mild non-proliferative diabetic retinopathy without any macular involvement,Renal function: estimated glomerular filtration rate (eGFR) of 45 ml/min/1.73 m^2^ or higher (up to stage 3a classification of chronic kidney disease) [13],Non-smokers, or ex-smokers who have quit smoking for at least 12 months,Willingness to download the OPTIMUM smartphone application (app),Willingness to use the standard monitoring devices (blood pressure set, glucometer and weighing scale) which will synchronise with the OPTIMUM telemonitoring system according to the study protocol throughout the 6-month study period,

#### Exclusion criteria

Poorly controlled glycaemic control based on the latest HbA1c reading of more than 10%.Cognitive impairment based on a diagnosis of dementia or mild cognitive impairment in the EMR.Pre-existing retinal pathologies documented in the EMR: proliferative diabetic retinopathy (moderate to severe) or other retinal and macular or diseases.Pre-existing chronic kidney disease stage 3b, 4 or 5.Known peripheral vascular, coronary and cerebrovascular disease.Individuals with any end-stage disease with life prognosis of less than 2 years.Pregnant women.Self-declared reluctance or inability to commit to the entire study over 24 months.Self-declared reluctance to use the OPTIMUM smartphone app and the associated monitoring devices.Current enrolment in another trial involving therapeutic or non-therapeutic intervention which will interfere with the primary and secondary outcomes in this study.

### Recruitment

The potential patients who fulfil the eligibility criteria will be provided with an approved patient information sheet by the attending physician during their visit. Their queries and doubts will be addressed by the attending physician before their written endorsement of informed consent is obtained by a clinical research coordinator (CRC). The CRC will then administer standardised questionnaires to record their demographic and clinical data (Table 1) before randomisation. A total of $200 Singapore dollars in grocery vouchers will be given to each participant at recruitment and at each of the study visits to promote participant retention and complete follow-up (Fig. 1).

**Table 1 Tab1:**
[figure not shown]
SPIRIT flow diagram of the OPTIMUM trial study protocol

−*t*_1_, baseline assessment; *t*_0_, randomisation (month 0); *t*_6_, postintervention assessments (month 6); *t*_12_, follow up assessments (month 12); *t*_24_, follow-up assessments (month 24); *t*_*x*_, qualitative interviews

1. Demographics includes age, gender, ethnicity. Socioeconomic status includes housing type, employment status, marital status, living status (with children/domestic helper), household monthly income, citizenship and education level.

2. Only employment status will be collected. Other demographics and socioeconomic status will not be collected.

3. Medical history includes diagnosis of hypertension, years of being hypertensive, diagnosis of hyperlipidaemia, years of being hyperlipidaemic, diagnosis of retinopathy, nephropathy, neuropathy, diabetic foot complications, coronary arterial disease, hypoglycaemia, transient ischemic attack or stroke.

4. Years of being diabetic will be included in medical history.

5. Lifestyle survey includes smoking and alcoholic drinking habits and history.

6. Lipid panel includes LDL and HDL cholesterol, triglycerides.

7. All these data will be collected from patients’ medical records 1 month before the recruitment, or within 1 month after the recruitment if the past data is unavailable.

8. History of flu and pneumonia vaccination.

9. Vital signs include systolic and diastolic blood pressure, pulse rate, weight and height.

10. Oral diabetes medication compliance measured using the MARS 5 questionnaire and insulin compliance measured using MPR.

11. Well-being and confidence surveys include Michigan diabetes knowledge, self-care inventory, the international physical activity questionnaire (short) and EQ-5D-5L.

12. Diabetes distress survey using the Problem Areas in Diabetes Scale (PAID).

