### Intervention

A set of three Bluetooth-enabled devices, a weighing scale (Xiaomi Body Composition Scale 2), a glucometer (Accu-chek Guide set, Model 929 mmol/L) and an electronic blood pressure monitor (Smartfuture Medcheck Blood Pressure Monitor SFB01), will be allocated to each patient in the intervention arm for their sole use during the trial. The CRCs or nurses in the study team will induct these patients to the use of the three devices, and synchronise them with the OPTIMUM app. The patients will use the app to provide their responses to the health assessment questionnaires, which will then automatically transmit the data to the nurses for review.

Patients randomised to the control arm will continue with standard care as described previously and may continue using their own devices, if any, for their own monitoring. Patients randomised to the intervention arm are expected to perform the following tasks in the first 6 months after recruitment (Fig. 2).

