#### Tele-education

For a period of eight consecutive weeks post-enrolment, patients will receive weekly push reminders for self-monitoring via the OPTIMUM app, links to educational videos covering various aspects of T2DM management (understanding T2DM, eating healthily, alcohol and smoking advice, physical activity demonstrations, and having a healthy mindset). These videos aim to empower patients to improve their self-management of T2DM. After viewing each video, each patient will take a short quiz to test their knowledge related to the video content via the app.

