#### Laboratory data

Blood investigations are performed at the accredited on-site laboratory or central laboratory at Singapore General Hospital. They include:
Glycaemic control: HbA1c (onsite using the DCA® Vantage Analyser).Lipid panel (total cholesterol, HDL-cholesterol, triglycerides and calculated LDL-cholesterol) at central laboratory with the Roche® Cobas c702 machine using the enzymatic colourimetric method.Renal panel (serum electrolytes and creatinine levels) using the Roche® Cobas c702 machine in the central laboratory. The eGFR is computed using the Chronic Kidney Disease Epidemiology Collaboration (CKD-EPI) equation [18].Urine albumin and urine creatinine using the Beckman DXC700AU machine in the central laboratory.

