### Outcomes

#### Primary outcome measures

The primary outcome will be the mean HbA1c and magnitude of its change on enrolment and at 6 months in patients in the intervention arm compared with those in the control arm.

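### Table 1 footnote 7 lets some baseline data be collected up to a month after recruitment, when the intervention has begun; if HbA1c is among them, the change from enrolment is pulled towards no effect

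*Protocol article*

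**What the plan says.** Table 1 (SPIRIT flow diagram) labels -t1 as the baseline assessment and t0 as randomisation. Its footnote 7 gives a look-back of one month before recruitment for data drawn from medical records, with a fallback: "within 1 month after the recruitment if the past data is unavailable". The rows that carry this footnote are not visible.

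Under Recruitment, the coordinator's questionnaires cover "demographic and clinical data (Table 1) before randomisation". Under Intervention, "Patients randomised to the intervention arm are expected to perform the following tasks in the first 6 months after recruitment". Under Tele-education, "For a period of eight consecutive weeks post-enrolment, patients will receive weekly push reminders for self-monitoring via the OPTIMUM app".

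Under Primary outcome measures, "The primary outcome will be the mean HbA1c and magnitude of its change on enrolment and at 6 months", compared between arms. Eligibility rests on the most recent reading: "Latest glycaemic control based on HbA1c reading between 7% and 10" per cent, with no limit on how old it may be. Under Laboratory data, HbA1c is run at the clinic ("Glycaemic control: HbA1c (onsite using the" named analyser), whereas lipid, renal and urine tests go to the central laboratory.

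**The concern.** A baseline has to be free of treatment. Footnote 7 permits a value obtained up to a month after recruitment, and nothing in the article delays the intervention until such values are in, marks them, or confines the fallback to items that treatment cannot alter. About four of the eight weekly tele-education contacts can fall inside that month, alongside self-monitoring and nurse calls.

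If HbA1c is one of the items, the enrolment value in the intervention arm may already include part of the treatment effect. Subtracting it from the 6-month value understates the change in that arm only, so the between-arm contrast moves towards zero. A larger sample would not remove this. Because the trial is open-label, how often late collection occurs could also differ by arm.

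**Working it through.** **Timing, set side by side**

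1. Table 1 legend: baseline (-t1) precedes randomisation (t0).
2. Table 1, footnote 7: some record data may be collected up to one month after recruitment.
3. Randomisation section: allocation follows written consent. Intervention and Tele-education sections: activity is counted from recruitment or enrolment.

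Items 1 and 2 conflict for any row carrying the footnote. By item 3, the late window overlaps treatment.

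**Which items could be late**

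- The footnote sits between the lipid-panel note (6) and the vaccination note (8). That suggests laboratory or record items but does not establish HbA1c.
- Screening section: patients are identified from those with the fasting panel and approached at the review a week later. Setting and participants lists that panel as electrolytes, lipids, liver tests and urine albumin-creatinine ratio. Those values are therefore about one week old, inside the look-back.
- HbA1c is not on that list. It is tied to a consultation every 3–6 months. A patient can therefore have a recent panel, an eligible but older HbA1c, and none in the preceding month.

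**The plan's own sample size**

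Inputs (Sample size calculation): difference 0.5; SDs 1.4 and 1.3; two-sided 5%; 80% power; 1:1; 30% dropout.

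- Pooled SD = √((1.4² + 1.3²)/2) = √1.825 = 1.351.
- n per arm = 2 × 1.825 × (1.960 + 0.842)² / 0.5² ≈ 114.6, so 115.
- Power at 115 = Φ(0.5 / (1.351 × √(2/115)) − 1.960) = 80.1%.
- 115 / 0.70 = 164.3, so 165 per arm and 330 in total.

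The stated figures reproduce; none is in dispute.

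**Illustration of the bias**

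Let f be the share of intervention patients whose baseline HbA1c is taken after the start, and s the share of the 6-month effect already present at that point. The expected contrast in change is 0.5 × (1 − f × s). The document gives neither f nor s, so both are assumed. SD is held at 1.351.

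| f | s | Contrast | Power, 115/arm | Power, 165/arm |
|---|---|---|---|---|
| 5% | 10% | 0.4975 | 79.8% | 91.7% |
| 10% | 25% | 0.4875 | 78.1% | 90.6% |
| 20% | 10% | 0.49 | 78.5% | 90.9% |
| 20% | 25% | 0.475 | 76.0% | 89.1% |
| 20% | 50% | 0.45 | 71.4% | 85.7% |

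The first and last rows are the ends of the range considered. The 115 column applies if the full 30% loss, which the plan allows over 24 months, has already happened by month 6. The 165 column applies if nobody has been lost by then. The comparison of 6-month means does not use the baseline value, so its contrast stays at 0.5 in every row.

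**The case against.** The strongest reply is that the footnote may never touch HbA1c. The rows are unseen, HbA1c is run on site on its own route, and enrolment takes place at a medical review, where an HbA1c may well be at hand. The fallback also applies only when past data are unavailable. Every eligible patient has some HbA1c reading, so if unavailable means no value at all, the fallback is never triggered for HbA1c; it is triggered only if the word means none within the month. All of this stands as a limit on how often the problem would arise. It does not remove the problem, because the wording permits either reading.

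Recruitment also offers weaker support than it first seems to: "The CRC will then administer standardised questionnaires to record their demographic and clinical data (Table 1) before randomisation" concerns questionnaires, while footnote 7 concerns medical records. The firm conflict is within Table 1 itself.

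A reader might infer more than the document supports:

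- That renal and lipid baselines are equally exposed. The pre-screening route largely protects them.
- That a late out-of-range HbA1c makes a randomised patient ineligible. Eligibility is judged on the latest reading at screening, before consent, and a later value does not undo it.
- That a baseline-adjusted analysis is biased. The Statistical analysis section describes a two-sample t test (or a non-parametric test) and states no baseline-adjusted model.
- That power will fall to about 71%. That figure needs the least favourable pair of assumptions and only 115 evaluable patients per arm at month 6.

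**Conclusion.** The point holds in a limited form. Footnote 7 conflicts with the table's own order of baseline before randomisation and, followed literally, can place an on-treatment value in the baseline. Whether HbA1c is affected is an inference from the footnote's position and from the undated qualifying reading. If it is, the change-from-enrolment part of the primary outcome is biased towards no effect, while the 6-month mean comparison is untouched.

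The size cannot be obtained from the document and is probably small. Under the assumed ranges the loss is 0.0025 to 0.05 of the planned 0.5 difference. This is a case for a low-cost tightening of the wording; it does not show that the trial is underpowered or its primary result compromised.

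**What to change.** Reword footnote 7 so that baseline measures that treatment can change, above all HbA1c, must be dated on or before randomisation. Where no value exists within the one-month look-back, take the on-site HbA1c, and draw any other missing bloods, at the recruitment visit before the envelope is opened. Keep the post-recruitment window only for items that treatment cannot change, such as past history. Flag any value that is nevertheless dated after randomisation and keep it out of change scores.

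The sample size does not change. The cost is a slightly longer recruitment visit for a minority of patients. Excluding late values leaves those patients without a change score, but they remain in the 6-month mean comparison, and there should be few of them once the footnote is reworded.
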